# Statistical Analysis Plan

## 1. Introduction

Opioid Use Disorder (OUD) represents an addictive condition characterized by intense cravings for opiate substances, increased tolerance, difficulty in reducing usage, and notable withdrawal symptoms upon cessation. According to the "World Drug Report 2021", as of 2020, approximately 275 million individuals globally were drug users, with opiate drugs still contributing the most to the disease burden caused by illicit substances.

Methadone, an artificially synthesized opioid medication, is the cornerstone of methadone maintenance treatment (MMT), a community-based substitution therapy for opioid substances. The effectiveness of MMT in treating OUD is unquestionable, but associated issues have become increasingly apparent. As a synthetic opioid medication, methadone carries addictive potential and the risk of misuse. As the duration of treatment progresses, tolerance to methadone also increases, necessitating higher doses to maintain therapeutic effects, thereby raising the risk of overdose-related fatalities. Moreover, reports indicate a persistent rise in constipation among MMT clients, with insomnia detection rates ranging from 58.2% to 85.8%. Patients experience varying degrees of anxiety, depression, and other symptoms for a considerable period, while MMT-related sexual dysfunction is also prevalent. MMT clients have a need to reduce the methadone dose, but the effectiveness of reducing the methadone dose by themselves is limited. Currently, there is still a lack of measures to promote the reduction of methadone dosage while reducing its risk of opioid relapse.

Acupuncture, as an integral component of traditional Chinese medicine, boasts a history spanning thousands of years in disease treatment. Several studies have identified the potential role of acupuncture in improving opioid dependence by reducing opioid use and diminishing craving. In general, although there have been several studies focusing on acupuncture as an adjunct treatment for drug addiction,

they have predominantly consisted of small-sample clinical trials without the inclusion of sham acupuncture as a control. Consequently, there is a compelling need to undertake high-quality prospective RCT incorporating sham acupuncture as a control in order to substantiate and affirm the efficacy and safety of acupuncture in MMT, thereby providing more persuasive evidence.

## **2. Study Objectives and Hypothesis**

The aim of this study is to evaluate the efficacy and safety of manual acupuncture intervention for MMT clients through a multicenter clinical randomized controlled trial, comparing it with non-penetrating sham acupuncture.

## **3. Design**

### **3.1 Overview**

This parallel-arm, patient-blinded, multicenter, randomized, controlled trial will be performed to demonstrate the safety and effectiveness of manual acupuncture intervention for MMT clients.

### **3.2 Eligibility Criteria**

#### **3.2.1 Inclusion Criteria**

Patients will be included if they have:

- Diagnosed as opioid dependence according to the fifth edition of the Diagnostic and Statistical Manual of Mental Disorders (DSM-5) (Appendix 1);
- Aged between 18-65 years;
- Received MMT for more than 6 weeks;
- Demand for methadone tapering;
- Not having received any kind of acupuncture therapy during the previous 3 months.

#### **3.2.2 Exclusion Criteria**

Patients will be excluded if they have:

- Serious heart, liver, lung, or kidney diseases;
- Syphilis or AIDS;
- Severe digestive disease or malnutrition;
- Severe primary hematological disorders;
- Received other treatment that may affect the efficacy evaluation of the present intervention;
- Infection, inflammation, scar, or injury close to the site of the selected acupoints;
- Pregnancy, or plans for pregnancy;
- Had a history of mental illness other than drug dependence.

In addition, all patients are instructed not to take any other medications aiming at alleviating withdrawal symptoms, improving sleep quality, or managing depression and anxiety during the study, in order to avoid initiating other interventions. Patients who consume such medications are excluded from the study.

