To investigate the relationship between daily consumption of methadone and the intensity of opioid craving over a 20-week period, scatter plots are employed as a visual representation in this study with the x-axis representing the opioid craving VAS and the y-axis representing the daily consumption of methadone. The resulting scatter plot allows for the examination of the correlation between these two variables, providing insights into the potential influence of methadone intake on opioid craving levels over time.

Efficacy analyses will be performed for both the full analysis set (FAS) population and the per-protocol set (PPs) population. The FAS population will consist of all randomized patients who received at least one treatment. In a PPs analysis, only patients who complete all the clinical trials according to the protocol are counted towards the results. Besides, the PPs population in our research will meet these criteria: the experimental treatment requirements; the main variables can be determined; no missing baseline variables; no major violation of the test scheme. Safety analyses will be performed on the safety population, which will be comprised of all randomized subjects who have been administered at least one treatment. A PP analysis is carried out as a sensitivity analysis compared with the results obtained using the FAS analysis. When the PPs and FAS analysis conclusions are not the same, it is necessary to analyze the possible reasons and discuss them.

Primary outcomes used 2-sided tests at the 2.5% significance level. All other statistical tests are 2-sided at the 5% significance level.

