### **6.2 Study Populations**

All randomised patients who receive at least one session of acupuncture intervention and at least one efficacy measure will be included in the full analysis set. All randomised patients who completed all the intervention and 20 weeks follow-up assessments will be included in per-protocol analysis set.

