### **7.2 Missing Data**

We will use multiple imputation method under the missing at random (MAR) assumption for the primary and secondary outcome with missing data. Multiple imputations use the observed data to fill in the missing values repeatedly to give rise to multiple "pseudo-complete" datasets. We will perform the imputation of missing data 100 times using regression imputation, employing the SAS procedure Proc MI process. For each time point, measurements of primary and secondary outcomes are imputed using groups, baseline measurements, and measurements prior to the time point as covariates in regression models. The estimated values are set as integers, and 100 different datasets are generated. By calculating the median of all estimated values for missing data, the 100 imputed datasets are merged into one.

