### **7.5 Sensitivity Analyses for the Primary Outcomes**

A PP analysis is carried out as a sensitivity analysis compared with the results obtained using the FAS analysis. When the PPs and FAS analysis conclusions are not the same, it is necessary to analyze the possible reasons and discussion them.

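### Randomised participants who take medication for withdrawal, sleep, depression or anxiety are excluded from the study without a stated place in the analysis, and the two full analysis sets differ

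*Combined protocol and SAP*

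**What the plan says.** Protocol 4.2 and SAP 3.2.2 carry the same rule. Patients are told not to take other medication aimed at withdrawal symptoms or at "improving sleep quality, or managing depression and anxiety during the study". The consequence follows: "Patients who consume such medications are excluded from the study". Neither document defines that exclusion.

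The full analysis set (FAS) has two definitions:

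- Protocol section 11: "The FAS population will consist of all randomized patients who received at least one treatment".
- SAP 6.2: randomised patients who "receive at least one session of acupuncture intervention and at least one efficacy measure will be included in the full analysis set".

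The per-protocol set also has two. SAP 6.2 says: "All randomised patients who completed all the intervention and 20 weeks follow-up assessments will be included in per-protocol analysis set". Protocol section 11 has a longer list, which includes the absence of a major protocol violation.

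On missing data, SAP 7.2 says: "We will use multiple imputation method under the missing at random (MAR) assumption". On sensitivity analysis of the primary outcomes, SAP 7.5 says: "A PP analysis is carried out as a sensitivity analysis compared with the results obtained using the FAS analysis". No other sensitivity analysis is named.

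**The concern.** The rule is printed under eligibility, but it acts on behaviour during the study, which means 8 weeks of treatment and 12 of follow-up after randomisation (protocol 3.1). It therefore removes randomised people because of something that happens afterwards.

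That event is not neutral. The four indications named are the domains of the four secondary scales, and one PSQI component scores the use of sleep medication (protocol 6.2.2). The primary outcomes are dose reduction and craving, so for them the link is indirect. It is plausible, though, because Appendix 2 lets a taper be halted or reversed when adverse reactions occur.

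If symptoms lead to medication at different rates in the two arms, the people still observed at week 8 or week 20 are no longer the groups that were randomised. Faster tapering could provoke symptoms in one arm, and lack of benefit could do so in the other. A later decision about who counts as excluded could also be taken with the data in view.

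**Working it through.** **1. Who is analysed, from the text.** Take a participant who has had at least one session, has an efficacy measure, and takes a sleep medicine in week 5.

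| Rule | Result |
|---|---|
| Protocol 4.2, SAP 3.2.2 | Excluded from the study |
| Protocol section 11, FAS | Kept: has had one treatment |
| SAP 6.2, FAS | Kept: has one session and one efficacy measure |
| SAP 6.2, per-protocol | Out only if treatment or the 20-week assessments are incomplete; no medication criterion |
| Protocol section 11, per-protocol | Out if the use counts as a major violation |

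Two readings fit: (a) deletion from the analysis, or (b) membership of the FAS with follow-up stopped. Under (b) the later values are imputed from group, baseline and earlier measurements (SAP 7.2). PSQI, BDI-II and BAI are collected only every four weeks, so worsening that prompts medication between visits may never enter that model. The per-protocol analysis is narrower still and cannot test the assumption.

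**2. Inputs for an illustration.** The plan states no figure on this point. The sham responder rate of 36%, the acupuncture rate of 70% and 50 participants per arm come from protocol section 10. That sample size is not in dispute: the pooled two-proportion formula at two-sided 5% and 90% power gives 44 per group against the stated 42, and 42/0.85 = 49.4, rounded up to 50. The exclusion rates below are assumptions.

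**3. Deletion reading, no true effect, only non-responders removed.** If a fraction x of the whole arm is removed, the observed rate is 0.36/(1 − x).

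- 15% against 5%: 0.36/0.85 = 42.4%; 0.36/0.95 = 37.9%; false gap 4.5 points.
- 20% against 5%: 0.36/0.80 = 45.0%; 37.9%; false gap 7.1 points.
- Equal removal gives equal rates and no gap.

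**4. Same reading, rates expressed among non-responders.** If a fraction e of the non-responders is removed, the observed rate is 0.36/(0.36 + 0.64(1 − e)).

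- 0% against 10%: 36.0% and 0.36/0.936 = 38.5%; gap 2.5 points.
- 10% against 30%: 38.5% and 0.36/0.808 = 44.6%; gap 6.1 points.

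With 50 randomised per arm and a normal approximation, the chance of rejection at the nominal two-sided 2.5% level is about 3.0% in the first case and 5.0% in the second.

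**5. Planned effect (70% against 36%).** Remove 10% of acupuncture and 30% of sham non-responders: 0.70/0.97 = 72.2% against 44.6%. The 34-point difference becomes 27.6 points.

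**6. Sign.** If those removed were all responders, 15% against 5% of the arm would give (0.36 − 0.15)/0.85 = 24.7% and (0.36 − 0.05)/0.95 = 32.6%, a gap of 7.9 points the other way. The direction depends on which arm loses more and on who is lost.

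**7. The two FAS definitions.** They differ only by the efficacy-measure condition. It depends on data being available, not on the value recorded. Methadone dose is recorded daily from baseline (protocol 6.1.1), so few people are likely to fail it. The SAP does not say whether a baseline value counts.

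**The case against.** The strongest reply is that deletion is nowhere stated. A reader might infer from the exclusion sentence that medication users are dropped from the efficacy analysis. The sections that define who is analysed contain no such exclusion, and both FAS definitions keep a treated user (the SAP's if one efficacy measure exists). This stands. What the documents show is an exclusion rule with an undefined consequence.

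Three further inferences also go too far.

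- That the SAP's efficacy-measure condition selects on outcome. It selects on availability of data.
- That imputation under missing at random cannot help. Dropout that depends on symptoms already recorded and used in the imputation model is compatible with that assumption. The valid worry is narrower: symptoms that arise between visits, with no analysis that departs from the assumption.
- That the per-protocol analysis already deals with concomitant medication. The SAP's version has no medication criterion, and any per-protocol set is itself selected after randomisation.

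The illustration is also open to challenge. It models deletion, whereas the written plan imputes. It assumes that everyone removed is a non-responder, although tapering quickly enough to provoke symptoms would tend to remove responders. The 20% against 5% case averages 12.5%, which is most of the 15% attrition planned for all causes. These points limit the size that can be claimed. They do not remove the problem: if the exclusion is followed, later data are lost for symptom-related reasons on either reading.

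**Conclusion.** The concern holds in a limited form. The plan excludes randomised participants for an event tied to the measured symptoms and does not say what becomes of their follow-up and data. Nothing else in the plan protects the comparison from that loss. The FAS mismatch is a real inconsistency but probably a small one.

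No size can be derived from the documents. The false gaps of 2.5 to 7.1 points are worst cases for selective loss of non-responders. They rest on deletion, on assumed and unequal exclusion rates, and on a 36% true response in both arms. Under imputation the effect should be smaller to the extent that earlier measurements predict later ones. With equal removal there is no false gap under the null, and the true direction is unknown. The case for acting is that the ambiguity can be closed cheaply and in advance.

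**What to change.** 1. Leave the medication instruction as it is. In protocol 4.2 and SAP 3.2.2, replace the exclusion sentence, for people already randomised, with a statement of this kind: participants who take such medication remain in follow-up and in the full analysis set as randomised; use is recorded and reported by arm; it removes them only from the per-protocol set.
2. Use one FAS in protocol section 11 and SAP 6.2, without the efficacy-measure condition. The one-treatment condition, which both documents share, can stay.
3. Reconcile the two per-protocol definitions and add the medication criterion to SAP 6.2.

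This concerns follow-up and analysis only, not which medication is allowed. The cost is wording, plus visits that are already scheduled. Methadone dose is recorded daily to week 20, so that outcome should remain obtainable for anyone still attending. The downside is some dilution of the estimate by concomitant medication, which the by-arm report makes visible. A useful addition, where later data are still missing, would be one sensitivity analysis that does not rely on missing at random.

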#### 4. Study Schema

|                  | STUDY PERIOD                   |            |                                                                                    |   |   |   |   |   |   |   |           |    |    |
|------------------|--------------------------------|------------|------------------------------------------------------------------------------------|---|---|---|---|---|---|---|-----------|----|----|
|                  | Enrolment                      | Allocation | Treatment phase                                                                    |   |   |   |   |   |   |   | Follow-up |    |    |
| Timepoint (week) | −1                             | 0          | 1                                                                                  | 2 | 3 | 4 | 5 | 6 | 7 | 8 | 12        | 16 | 20 |
| ENROLLMENT:      | ×                              |            |                                                                                    |   |   |   |   |   |   |   |           |    |    |
|                  | ×                              |            |                                                                                    |   |   |   |   |   |   |   |           |    |    |
|                  | ×                              |            |                                                                                    |   |   |   |   |   |   |   |           |    |    |
|                  |                                | ×          |                                                                                    |   |   |   |   |   |   |   |           |    |    |
| INTERVENTIONS:   |                                |            |                                                                                    |   |   |   |   |   |   |   |           |    |    |
|                  |                                |            | [figure not shown] |   |   |   |   |   |   |   |           |    |    |
|                  |                                |            | [figure not shown] |   |   |   |   |   |   |   |           |    |    |
| ASSESSMENTS:     |                                |            |                                                                                    |   |   |   |   |   |   |   |           |    |    |
|                  | Daily Consumption of Methadone | ×          |                                                                                    | × |   | × |   | × |   | × | ×         | ×  | ×  |
|                  | opioid craving VAS             | ×          |                                                                                    | × |   | × |   | × |   | × | ×         | ×  | ×  |
|                  | COWS                           | ×          |                                                                                    | × |   | × |   | × |   | × | ×         | ×  | ×  |
|                  | BAI                            | ×          |                                                                                    |   |   | × |   |   |   | × | ×         | ×  | ×  |
|                  | BDI-II                         | ×          |                                                                                    |   |   | × |   |   |   | × | ×         | ×  | ×  |
|                  | PSQI                           | ×          |                                                                                    |   |   | × |   |   |   | × | ×         | ×  | ×  |
|                  | ADVERSE EVENTS:                |            |                                                                                    | × | × | × | × | × | × | × | ×         | ×  | ×  |

Abbreviations: Opioid craving VAS, the visual analog scale for opioid craving; COWS, Clinical Opioid Withdrawal Scale; PSQI, Pittsburgh Sleep Quality Index; BDI-II, The Beck Depression Inventory-II; BAI, The Beck Anxiety Inventory.

**Figure 1:** Schedule of enrolment, interventions, and assessments

## **5. Efficacy and Safety Outcomes**

### **5.1 Primary Outcomes**

One primary outcome is the rate of methadone dose reduction, defined as the proportion of participants who achieve a reduction in methadone dose of  $\geq 20\%$  compared to baseline after 8 weeks of intervention. The other primary outcome is the opioid craving using a visual analog scale for drug craving marking on a 100-millimetre line in proportion to their craving from 0 (no craving) to 100 (strong craving)

### **5.2 Secondary Outcomes**

- Clinical Opioid Withdrawal Scale (COWS)
- Pittsburgh sleep quality index (PSQI)
- The beck depression inventory-II (BDI-II)
- The beck anxiety inventory (BAI)
- Urine test

## **6. Statistical Considerations**

### **6.1 Study Hypothesis**

The primary study hypothesis is that manual acupuncture is more efficacy than sham acupuncture in reducing methadone dose and opioids craving in MMT clients.

### **6.2 Study Populations**

All randomised patients who receive at least one session of acupuncture intervention and at least one efficacy measure will be included in the full analysis set. All randomised patients who completed all the intervention and 20 weeks follow-up assessments will be included in per-protocol analysis set.

## **7. Statistical Analysis**

### **7.1 Summary Statistics**

Continuous variables are reported as the mean with standard deviation or median and interquartile range. Categorical variables are described as numbers and percentages. Continuous variables will be compared using a two-sample t-test or Wilcoxon rank-sum test if data show serious deviations from a normal distribution. Categorical data or ordinal data will be compared using a Wilcoxon rank-sum test, chi-square test or Fisher's exact test, as appropriate.

### **7.2 Missing Data**

We will use multiple imputation method under the missing at random (MAR) assumption for the primary and secondary outcome with missing data. Multiple imputations use the observed data to fill in the missing values repeatedly to give rise to multiple "pseudo-complete" datasets. We will perform the imputation of missing data 100 times using regression imputation, employing the SAS procedure Proc MI process. For each time point, measurements of primary and secondary outcomes are imputed using groups, baseline measurements, and measurements prior to the time point as covariates in regression models. The estimated values are set as integers, and 100 different datasets are generated. By calculating the median of all estimated values for missing data, the 100 imputed datasets are merged into one.

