## 11. Statistical Analysis

Statistical analysis will be performed by the Clinical Research and Big Data Laboratory, South China Research Center for Acupuncture and Moxibustion, Guangzhou University of Chinese Medicine. The statistician will be blinded to group allocation until final unblinding. SAS 9.4 will be utilized for data analysis. Missing data are filled by using multiple imputation.

Continuous variables are reported as the mean with standard deviation or median and interquartile range. Categorical variables are described as numbers and percentages using  $\chi^2$  test or Fisher's exact test. Longitudinal measures through 20 weeks (8 weeks of intervention and 12 weeks of follow-up) are analyzed for all outcomes. The analysis of proportion of participants with at least 20% reduction from baseline in the amount of methadone dose is performed using a generalized linear mixed-model. For opioid craving VAS and all secondary outcomes, analysis is conducted utilizing a linear mixed-model. For above models, values measured at baseline are used as covariates; intervention assignment, visit and intervention  $\times$  visit interaction are as fixed effects; and treatment centre and centre  $\times$  intervention interaction are as random effects. We assessed the poolability of treatment effects across centres by including centre  $\times$  intervention interaction in the model. If *P*-values corresponding to the centre  $\times$  intervention interaction term for both primary endpoints are greater than 0.10, the treatment effect is homogenous across centres [59].

Dynamic data will be demonstrated on the reduction in the methadone consumption and the opioid craving VAS score in the figures, separated by the manual acupuncture and sham group. Each row in the figures represents the reduction dose of

the daily consumption of methadone (the opioid craving VAS score) for one participant. Individuals who discontinue participation early appear at the bottom of each plot, whereas those with complete data appear at the top.

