### **7.4 Analyses for Outcomes**

The analysis of proportion of participants with at least 20% reduction from baseline in the amount of methadone dose is performed using a generalized linear mixed model. For opioid craving VAS and all secondary outcomes, analysis is conducted utilizing a

linear mixed-model. For above models, values measured at baseline are used as covariates; intervention assignment, visit and intervention  $\times$  visit interaction are as fixed effects; and treatment centre and centre  $\times$  intervention interaction are as random effects. Before building the final model, we assess the poolability of treatment effects across centres by including centre  $\times$  intervention interaction in the model. If *P*-values corresponding to the interaction term for both primary endpoints are greater than 0.10, the treatment effect is homogenous across centres and centre  $\times$  intervention interaction will not be included in the final model. Primary outcomes use 2-sided tests at the 2.5% significance level. All other statistical tests are 2-sided at the 5% significance level. Dynamic data on the reduction in the methadone consumption and the opioid craving VAS score will be demonstrated in the figures, separated by two groups. Each row in the figures represents the reduction dose of the daily consumption of methadone (the opioid craving VAS score) for one participant. To investigate the relationship between daily consumption of methadone and the intensity of opioid craving over a 20-week period, scatter plots will be employed as a visual representation in this study with the x-axis representing the opioid craving VAS and the y-axis representing the methadone dose. The resulting scatter plot allows for the examination of the correlation between these two variables, providing insights into the potential influence of methadone intake on opioid craving levels over time.

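### The imputation model in SAP 7.2 leaves out later visits and centre, a small inefficiency that mainly touches intermittent gaps in the craving VAS and the secondary scales

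*Combined protocol and SAP*

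**What the plan says.** SAP 7.2 sets the assumption and scope: "We will use multiple imputation method under the missing at random (MAR) assumption for the primary and secondary outcome with missing data". The method is stated as "We will perform the imputation of missing data 100 times using regression imputation, employing the SAS procedure Proc MI process", and at each time point the outcomes are "imputed using groups, baseline measurements, and measurements prior to the time point as covariates in regression models". Protocol section 11 says only "Missing data are filled by using multiple imputation" and names no predictors, so it does not supply what SAP 7.2 leaves out.

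The analysis uses more than the imputation does. Protocol section 11 states: "Longitudinal measures through 20 weeks (8 weeks of intervention and 12 weeks of follow-up) are analyzed for all outcomes". In SAP 7.4 the models take the baseline value, intervention, visit and their interaction ("values measured at baseline are used as covariates; intervention assignment, visit and intervention" × visit). The sentence continues with "fixed effects; and treatment centre and centre" × intervention as random effects. The centre × intervention term is tested against P = 0.10 and dropped from the final model if both primary outcomes pass.

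**The concern.** An imputation model should normally contain at least the terms of the analysis model, plus observed data that predict the missing value. Two sets of terms are absent here.

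- **Later visits.** A forward-only chain suits participants who leave and never return. For someone who misses week 8 and attends at week 12, it discards an observed value of the same outcome. Missing at random is also easier to defend when the model conditions on everything observed.
- **Centre.** Values imputed without centre tend to be drawn towards the all-centre mean. That could weaken the between-centre differences which the poolability test in SAP 7.4 is meant to examine.

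At stake are a little precision at week 8 and consistency between imputation and analysis.

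**Working it through.** The plan gives no figure on this point to reproduce, and no between-visit correlations, so the correlations below are assumptions shown as a range.

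**Inputs from the documents**
- Craving VAS visits: weeks 0, 2, 4, 6, 8, 12, 16, 20 (protocol 6.1.2 and Figure 4). The visit before week 8 is 2 weeks away and the one after it is 4 weeks away.
- VAS difference 10, SD 8, 50 per group, about 15% attrition (protocol section 10). The rate of intermittent gaps is not given.

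**Step 1: residual SD of one missed week-8 value, autoregressive correlation**

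Let ρ be the correlation over 2 weeks, so weeks 8 and 12 correlate at ρ². With earlier visits only, the residual variance as a share of the total is 1 − ρ². With all visits it is (1 − ρ²)(1 − ρ⁴)/(1 − ρ⁶).

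At ρ = 0.8 this is 0.36 × 0.5904 / 0.7379 = 0.288, against 0.360. The SD ratio is √(0.288/0.360) = 0.894.

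| ρ per 2 weeks | R², earlier visits | R², all visits | SD ratio | Fall in residual SD |
|---|---|---|---|---|
| 0.5 | 0.25 | 0.29 | 0.976 | 2% |
| 0.7 | 0.49 | 0.56 | 0.928 | 7% |
| 0.8 | 0.64 | 0.71 | 0.894 | 11% |
| 0.9 | 0.81 | 0.86 | 0.857 | 14% |

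**Step 2: the same, equal correlation**

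With k predictors, R² = kρ²/(1 + (k − 1)ρ). Use k = 4 for the earlier visits (weeks 0 to 6) and k = 7 for all visits.
- ρ = 0.5: 1.00/2.5 = 0.400 against 1.75/4 = 0.4375. SD ratio √(0.5625/0.600) = 0.968, a fall of 3%.
- ρ = 0.8: 2.56/3.4 = 0.753 against 4.48/5.8 = 0.772. SD ratio √(0.228/0.247) = 0.960, a fall of 4%.

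**Step 3: standard error of the week-8 difference**

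If a fraction f of week-8 values is missing and all of those participants return, the variance of an arm mean is roughly proportional to R² + (1 − R²)/(1 − f). Take f = 0.15 and ρ = 0.8 (autoregressive):
- earlier visits only: 0.64 + 0.36/0.85 = 1.0635;
- all visits: 0.712 + 0.288/0.85 = 1.0508;
- SE ratio: √(1.0635/1.0508) = 1.006.

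Across the correlations in steps 1 and 2 the ratio lies between 1.002 and 1.006.

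**Step 4: simulation**

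3,000 trials, 50 per arm, SD 8, true difference 10, correlation 0.4 + 0.6 × 0.7^(weeks apart/2), missing week-8 values filled by regression prediction, all later visits observed.
- 15% missing, depending on week 6: SE 1.645 (earlier visits) against 1.637 (all visits), a change of 0.5%. Neither estimate is biased.
- 15% missing, depending on the week-8 value itself: the mean difference is −10.02 with full data, −9.72 with earlier visits and −9.77 with all visits. Bias is about 0.31 against 0.26 points of a 10-point effect.

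**Step 5: centre**

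No calculation is possible. The available text gives neither the number of centres nor a between-centre variance.

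**The case against.** The strongest reply is that nothing of consequence follows. A change of under 1% in the standard error will not alter a conclusion. Participants who drop out for good have no later data, and for them sequential regression on earlier visits is a standard method that loses nothing. This stands, and it keeps the point minor.

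Four stronger readings are tempting, and the documents do not support them.

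- *That both primary outcomes are affected alike.* Protocol 6.1.1 has participants attending daily for methadone, with consumption recorded to week 20. Someone who misses a study assessment but still attends the clinic has a recorded week-8 dose. The exposure lies mainly with the craving VAS and the secondary scales.
- *That the gain is as large as 11–22%.* Treating the eight visits as equally spaced gives those falls in residual SD at ρ = 0.5 and 0.8. The schedule has a double gap after week 8, and the corresponding figures are 2% and 11%.
- *That the estimate is biased.* If missingness depends only on group, baseline and earlier visits, leaving out later visits costs precision only. If it depends on the missing value itself, adding later visits removes only a small part of the bias.
- *That imputed values carry no centre information.* Each participant's own baseline and earlier scores bring centre differences in, at least partly.

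What remains is that observed data are discarded and a term of the analysis model is missing from the imputation model. Reading centre into the phrase about baseline measurements would be a stretch. The per-protocol sensitivity analysis in SAP 7.5 does not test the imputation, because SAP 6.2 limits that set to participants who completed all intervention and follow-up assessments.

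**Conclusion.** The point holds as a minor refinement. SAP 7.2 omits later visits and centre from the imputation, while the plan's own models use both. The cost is a small loss of precision for intermittent gaps, chiefly in the craving VAS and secondary scales, and an imputation not aligned with the analysis or its poolability test.

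The figures rest on assumed correlations. The under-1% result also takes every missed week-8 value to be followed by complete later data, which is the case most favourable to making the change. With permanent dropout among the missing, the gain is smaller. The direction is the same in every scenario examined. The effect of omitting centre remains unknown.

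The sentence "By calculating the median of all estimated values for missing data, the 100 imputed datasets are merged into one", also in SAP 7.2, is a separate and more serious matter, because it removes the between-imputation variance.

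**What to change.** In SAP 7.2, replace the forward-only regression with a PROC MI specification suited to non-monotone gaps, for example fully conditional specification. Use as predictors group, all visits of the same outcome (weeks 0 to 20) and centre.

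Keep the model small. Enter group as a covariate rather than fitting each arm separately, and add at most the same-visit value of the other primary outcome. Separate models by arm with every visit of both primary outcomes would mean 15 or more predictors (7 other visits plus 8 of the other outcome, before centre) in about 50 participants, which invites overfitting.

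The cost is a short edit to the SAP and the program, with no new data and no change of design. The downside is a few more terms, so convergence and overfitting must be checked. The median merge needs its own correction: analyse each imputed dataset and combine the results with Rubin's rules.
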